## Abstract

**Background:**

Patients undergoing vascular surgery procedures constitute a ‘high-risk’ group. Fatal and disabling perioperative complications are common. Complications arise via multiple aetiological pathways. This mechanistic redundancy limits techniques to reduce complications that target individual mechanisms, for example, anti-platelet agents. Remote ischaemic preconditioning (RIPC) induces a protective phenotype in at-risk tissue, conferring protection against ischaemia-reperfusion injury regardless of the trigger. RIPC is induced by repeated periods of upper limb ischaemia-reperfusion produced using a blood pressure cuff. RIPC confers some protection against cardiac and renal injury during major vascular surgery in proof-of-concept trials. Similar trials suggest benefit during cardiac surgery. Several uncertainties remain in advance of a full-scale trial to evaluate clinical efficacy. We propose a feasibility trial to fully evaluate arm-induced RIPC’s ability to confer protection in major vascular surgery, assess the incidence of a proposed composite primary efficacy endpoint and evaluate the intervention’s acceptability to patients and staff.

**Methods/Design:**

Four hundred major vascular surgery patients in five Irish vascular centres will be randomised (stratified for centre and procedure) to undergo RIPC or not immediately before surgery. RIPC will be induced using a blood pressure cuff with four cycles of 5 minutes of ischaemia followed by 5 minutes of reperfusion immediately before the start of operations. There is no sham intervention. Participants will undergo serum troponin measurements pre-operatively and 1, 2, and 3 days post-operatively. Participants will undergo 12-lead electrocardiograms pre-operatively and on the second post-operative day. Predefined complications within one year of surgery will be recorded. Patient and staff experiences will be explored using qualitative techniques. The primary outcome measure is the proportion of patients who develop elevated serum troponin levels in the first 3 days post-operatively. Secondary outcome measures include length of hospital and critical care stay, unplanned critical care admissions, death, myocardial infarction, stroke, mesenteric ischaemia and need for renal replacement therapy (within 30 days of surgery).

**Discussion:**

RIPC is novel intervention with the potential to significantly improve perioperative outcomes. This trial will provide the first evaluation of RIPC’s ability to reduce adverse clinical events following major vascular surgery.

**Trial Registration:**

www.clinicaltrials.gov NCT02097186 Date Registered: 24 March 2014

## Background

Ischaemic preconditioning is a phenomenon whereby a brief period of nonlethal ischaemia in a tissue renders it resistant to the effects of a subsequent much longer ischaemic insult. It was first described in the canine heart [1]. Subsequent clinical trials showed that ischaemic preconditioning reduced heart muscle damage following coronary artery bypass grafting [2] and liver dysfunction following hepatic resection [3]. Following cardiac surgery, it is associated with a reduction in critical care stay, arrhythmias and inotrope use [4]. However, ischaemic preconditioning requires direct interference with the target tissues’ blood supply, limiting its clinical utility. Further experimental work suggested that brief ischaemia in one tissue, such as the kidneys, could confer protection on distant organs such as the heart [5]. A similar effect was observed after transient skeletal muscle ischaemia [6]. This effect is referred to as ‘preconditioning at a distance’ or ‘remote ischaemic preconditioning’ (RIPC).

Patients requiring major vascular surgery for end-stage vascular disease constitute a high-risk surgical cohort. Perioperative complications such as myocardial infarction, cerebrovascular accident, renal failure and death are common [7,8]. Multiple potential mechanisms may lead to these complications. For example, myocardial injury may result from systemic hypotension leading to reduced flow across a tight coronary artery stenosis or, alternatively, it may arise due to acute occlusion when an unstable plaque ruptures. Most strategies aimed at perioperative risk reduction target a single potential mechanism. Thus, for example, beta-blockade may prevent myocardial injury due to overwork, but cannot prevent acute coronary occlusion. There is a requirement for a simple, effective intervention that protects tissues against injury via multiple different mechanisms. Remote ischaemic preconditioning (RIPC) may be suitable.

### Proof-of-concept trials

To date, there have been five small trials of RIPC in patients undergoing major vascular surgery (Table 1). The results were mixed. An apparent beneficial effect of RIPC on renal function following open abdominal aortic aneurysm (AAA) repair in one trial [9] could not be replicated in a subsequent smaller study specifically designed to evaluate renal injury [10]. However, RIPC did reduce renal injury biomarkers following elective endovascular aneurysm repair (EVAR) [11]. In carotid endarterectomy patients, RIPC had no significant effect on subclinical cerebral injury, as determined by saccadic latency deteriorations [12]. However, this trial was rendered underpowered by a high level of patient withdrawals. More recently, a further trial conducted in patients undergoing open AAA repair reported that RIPC reduced markers of pulmonary and intestinal injury [13]. A number of additional small trials have assessed the potential value of RIPC in adult cardiac surgery, again with mixed results [2,14]. Most of these small phase 1 and 2a trials did not report clinical outcomes in any detail, focusing appropriately on biomarkers. Recently, a pooled analysis of some of these trials reported a significant reduction in post-operative troponin levels with RIPC [15]. Few of these studies reported clinical outcomes for example, death, myocardial infarction etc. Another recent meta-analysis examined the effect of RIPC on major clinical complications among 2,200 patients who underwent major cardiovascular surgery [16]. This review found no significant clinical benefit with RIPC, and the authors highlighted that this was likely to be related to a lack of sufficient sample size along with methodological heterogeneity in the individual studies.

**Table 1 Tab1:** **Summary of previous trials of remote ischaemic preconditioning (RIPC) in major vascular surgery**

**Trial reference**	**Number randomised**	**Operation type**	**Main findings**
Ali *et al*. Circulation [9]	82	Elective open AAA repair	RIPC produced significant reductions in post-operative troponin levels, myocardial infarctions and serum creatinine levels
Walsh *et al*. Vasc Endovasc Surgery [10]	40	Elective open AAA repair	RIPC had no significant effect on post-operative renal injury biomarkers.
Walsh *et al*. J Endovasc Ther [11]	40	Elective EVAR	RIPC produced significant reductions in post-operative biomarkers of renal injury
Walsh *et al*. Vasc Endovasc Surgery [12]	70	Elective carotid endarterectomy	RIPC had no significant effect on saccadic latency deteriorations or biomarkers of cardiac injury
Li *et al*. Anesthesiology [13]	62	Elective open AAA repair	RIPC produced significant reductions in biomarkers of intestinal and pulmonary injury

Legend: Table summarising previous trials of remote ischaemic preconditioning in major vascular surgery.

AAA – abdominal aortic aneurysm; EVAR – endovascular aneurysm repair; RIPC – remote ischaemic preconditioning.

At present, although exploratory studies are attractive, there is a notable lack of data on the effect of RIPC on clinical outcomes. Until hard data on clinical outcomes are available, RIPC cannot achieve a place in routine clinical practice.

### Rationale

It is pertinent to continue to investigate RIPC in the setting of major vascular surgery for several reasons. As mentioned earlier, perioperative risk is high in this group of patients and as such it is essential that risk reduction strategies be developed and maximised. Myocardial conditioning with RIPC seems especially attractive given the encouraging preclinical and proof of concept studies and given its benign risk profile. In contrast, other perioperative risk reduction strategies have limitations [17]: preoperative cardiac risk assessment is theoretically attractive but hard data on its efficacy are lacking [18]; pharmacological cardioprotection has largely been disappointing [19] with the exception of beta blockade in high risk groups [20]; prophylactic coronary revascularisation was shown to be often ineffective [21-24] and is only occasionally recommended [25,26]. Notably, the high perioperative morbidity rates in vascular surgery also confer a major practical advantage - as event rates are high, studies are likely to achieve adequate power with smaller sample sizes than would be necessary in lower risk groups.

Ideally, a clinical trial of RIPC in major vascular surgery would be powered to detect a significant reduction in ‘hard’ clinical endpoints (death, myocardial infarction etc.). A primary composite end-point (death, myocardial infarction, cerebrovascular accident, mesenteric ischaemia, and renal failure requiring renal replacement therapy) is proposed as the primary efficacy end-point for a phase 3 trial. Some pilot data from 40 patients randomised at University Hospital Limerick suggest that such an endpoint would occur in about 15% of patients. Assuming that 15% develop this endpoint, a minimum of 726 patients would be required in each arm to demonstrate a reduction to 10% (alpha 0.05, beta 0.8).

The proposed work builds on the previous trials conducted by the chief investigator in this area, a programme consistent with the *‘MRC Framework for the Design and Evaluation of Complex Interventions to Improve Health’*, which suggests core phases to the development of health interventions. This proposal describes the development and piloting phases of the MRC framework. Conducting a full-scale RCT, and economic evaluation, of remote preconditioning ‘standard care’ in this population is likely to require at least 1,500 participants and to be costly. As there are uncertainties regarding rates of eligibility, consent, participation in the intervention and retention for follow-up - and regarding the feasibility/acceptability of the intervention - this feasibility study is essential to inform the design and conduct of a larger scale study.

### Aims and objectives

This feasibility trial aims to address a number of key design uncertainties:With the exception of Li *et al*. [13], the previous vascular trials used the patient’s leg as the preconditioning stimulus while the cardiac trials almost always used the patient’s arm. The arm is preferable due to the much lower incidence of upper limb peripheral vascular disease. The use of arm RIPC in major vascular surgery patients should be assessed using a surrogate marker of efficacy in advance of a full-scale trial.Given the mixed results in the first four trials in major vascular surgery, a phase 2B trial to further evaluate potential efficacy using a surrogate marker is required to justify phase 3 work. This will also provide an accurate estimate of the likely effect size that can be expected in any phase 3 trial.Clinical trial capability in Ireland is underdeveloped relative to other Western countries. An examination of the feasibility of a large multicentre surgical trial particularly with respect to recruitment, drop-off rates, compliance, data collection and randomisation would be beneficial in advance of proceeding with a phase 3 trial.In order to evaluate the efficacy of RIPC in routine clinical practice in a reasonable timeframe at reasonable cost, we intend to use a composite primary efficacy endpoint in any full trial. Data regarding the incidence of this endpoint in major vascular surgery patients are lacking. This feasibility trial will provide robust data regarding this composite endpoint upon which to base power calculations for a phase 3 trial, should it appear justified from evaluation of the surrogate efficacy marker.

The single main research question for the feasibility trial, in terms of PICO (Population; Intervention; Comparator; Outcome) is as follows: ‘In adult patients undergoing elective major vascular surgery, does RIPC induced by brief arm ischaemia and reperfusion, when compared to control, reduce troponin leakage in the first 3 days post-operatively?’. Whilst powered to address this specific research question, this phase 2b trial will also provide insight into the feasibility of running a larger, phase 3 study, will provide data regarding the proposed composite primary efficacy endpoint and will evaluate the use of arm-generated as opposed to leg-generated RIPC in major vascular surgery patients.

## Methods/Design

### Study design

This is a randomised controlled pilot trial of the effect of RIPC induced by brief arm ischaemia and reperfusion on troponin levels in the first 3 days post-operatively in patients undergoing elective major vascular surgery. Patients are randomised to receive RIPC or act as controls. There is no sham intervention. The primary study endpoint is determined at 3 days post-operatively. Secondary study endpoints are evaluated at 30 days and one year post-operatively. Participant flow through the trial is described in Figure 1.

**Figure 1 Fig1:**
[figure not shown]
Participant flow through the trial. AAA – abdominal aortic aneurysm; CEA – carotid endarterectomy; ECG –electrocardiography; EVAR – endovascular abdominal aneurysm repair; PIL – patient information leaflet; RIPC – remote ischaemic preconditioning.

### Study setting

Patients undergoing scheduled major vascular surgery will be screened for eligibility in five vascular surgery units in the Republic of Ireland. Patients will receive routine perioperative care according to the current standard of care. During the study period, patients will be discharged home or to continuing care facilities within the geographic area.

### Participants

Patients undergoing elective carotid endarterectomy, open AAA repair, EVAR or surgical lower limb revascularisation (suprainguinal or infrainguinal) will be eligible for inclusion. Patients will be excluded if any of the following apply:PregnancySignificant upper limb peripheral arterial diseasePrevious history of upper limb deep vein thrombosisPatients on glibenclamide or nicorandil (these medications may interfere with RIPC)Patients with an estimated pre-operative glomerular filtration rate <30 mls/min/1.73 m^2^Patients with a known history of myocarditis, pericarditis or amyloidosisPatients undergoing fenestrated or branched EVAR.Patients with severe hepatic disease defined as an international normalised ratio >2 in the absence of systemic anticoagulationPatients with severe respiratory disease (for the trial, defined as patients requiring home oxygen therapy)Patients previously enrolled in the trial representing for a further procedurePatients with prior axillary surgery who are thus unsuitable for arm cuff inflation

### Informed consent and ethical approval

In each centre, potentially eligible patients will be selected from two patient groups: (1) outpatients awaiting major vascular surgery or (2) inpatients awaiting major vascular surgery. The process of obtaining informed consent will be conducted in compliance with the principals of good clinical practice and requirements of the approving research ethics committee and other regulatory requirements as appropriate. Consent to enter the study must be sought from each subject only after a full explanation has been given and time allowed for consideration. Signed subject consent will be obtained and a copy given to the subject. It is a right of the subject to refuse to participate or to withdraw at any time from the protocol without giving reasons and without prejudicing treatment. The trial has been reviewed and received approval from the Research Ethics Committees at University Hospital Limerick (final approval 1 May 2014), Cork University Hospital (ECM3 (j) 06/05/14), Waterford University Hospital (final approval 29 July 2014), St. James’s Hospital (2014-01List/05/19-02/2014-07 List25 (3), Beaumont Hospital (REC ref (14/01) and Galway University Hospital (Ref 22/12).

### Randomization, blinding and treatment allocation

Randomisation for the trial will be undertaken using a web-based randomisation system administered by the Health Research Board Clinical Research Facility Galway (HRBCRFG). The use of third-party randomisation will maintain allocation concealment. A unique trial number will be assigned at the time of randomisation. On the morning of surgery, patients will be randomised to one of two groups: either to RIPC or to the control arm. Randomisation will be stratified by centre using randomly selected blocks of 4, 6 and 8. In addition, each centre will be stratified by procedure. The randomisation will be accessed by a designated member of the research team at each site who will not be involved with data collection.

### Intervention

The intervention being tested is a simple intervention that can be undertaken using existing equipment. Immediately before the start of the operation, patients randomised to the RIPC arm will have a standard, CE-approved tourniquet cuff placed around one upper limb. It will then be inflated to a pressure of 200 mmHg for 5 minutes. For patients with a systolic blood pressure >185 mmHg, the cuff will be inflated to at least 15 mmHg above the patient’s systolic blood pressure. The cuff will then be deflated and the arm allowed to reperfuse for 5 minutes. This will be repeated so that each patient receives a total of four ischaemia-reperfusion cycles. There is no sham intervention for those in the control arm.

Previous trials of RIPC in cardiac surgery and percutaneous coronary interventions have generally used the arm as the source of the RIPC stimulus. Four previous trials of RIPC in major vascular surgery (Table 1) used the patients’ legs to generate the stimulus. In these trials, four patients in the RIPC arm developed post-operative critical lower limb ischaemia requiring intervention. The presence of known peripheral arterial disease also precluded the enrolment of about 20% of otherwise eligible patients. Given the success of upper limb RIPC in the cardiac and percutaneous coronary intervention (PCI) trials, the upper limb has been selected as the source for the RIPC stimulus in Preconditioning SAVES. In common with the ERICCA trialists [27], four cycles has been chosen in order to maximise the RIPC stimulus obtained and counteract three potential confounding issues: (i) the lower skeletal muscle bulk in the arm compared to the leg, (ii) the potential resistance to RIPC in aging and diabetic patients and (iii) the effect of variable volatile anaesthetic use.

There is a theoretical possibility that the RIPC stimulus obtained from the upper limb will be insufficient to produce a detectable effect due to the smaller skeletal muscle bulk compared to the lower limb. An adaptive trial design is therefore proposed, in which an interim analysis will be conducted after randomisation of 200 patients. If there is no evidence of potential benefit at this point, the stimulus will be adjusted to include three cycles of 5 minutes lower limb ischaemia alternating with 5 minutes reperfusion. The first lower limb ischaemic episode will commence as soon as the first upper limb ischemic period ends, so that both limbs are being preconditioned in parallel and no additional delay is introduced. If this augmented stimulus is introduced, bilateral ankle-brachial pressure indices <0.8 will be added to the exclusion criteria. The decision to amend the protocol will be made by the Trial Management Committee following advice from the Data Monitoring Committee.

The trial will be undertaken at multiple sites. It is intended to be a pragmatic clinical trial aiming to assess the potential adjunctive value of RIPC in routine clinical practice. Dedicated trial personnel will not be available on all the sites for each patients operation. Consequently, the SAVES trialists have elected not to include a sham intervention in the protocol. To do so would render the trial impractical at many sites.

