#### Primary safety endpoint

The intervention under investigation carries a theoretical risk of causing acute upper limb ischaemia or an upper limb deep vein thrombosis. Such an event has not been reported by any of the phase 1 and 2 trials of RIPC in cardiac patients. In addition, there is a theoretical risk of minor adverse events such as upper limb bruising. The primary safety endpoint will again be a composite of major life- or limb-threatening adverse events that could be attributed to the preconditioning stimulus. The components are:Acute upper limb ischaemiaAcute upper limb deep vein thrombosis

The components of the primary safety endpoint are defined as follows:Acute upper limb ischaemia, which is defined as the development of ischaemia in the arm used for the preconditioning stimulus requiring systemic anti-coagulation, radiological intervention or surgical intervention; andAcute upper limb deep vein thrombosis, which is defined as the development of thrombus within the subclavian, axillary or brachial vein confirmed in duplex ultrasound and in the same arm as used for the RIPC stimulus.

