**Table 2 Tab2:** **Definitions of other post-operative complications**

Respiratory failure	Unplanned initiation of assisted ventilation (CPAP or IPPV)
Transient ischaemic attack	New onset neurological deficit with lateralising signs, which resolves within 24 hours without evidence of cerebral bleeding or infarction on imaging and confirmed by a stroke physician or neurologist
Vascular graft occlusion	Occlusion of prosthetic or vein graft confirmed by imaging within 30 days of surgery
Wound infection	Erythema, purulent discharge, pyrexia, positive pathogenic organism on culture
Chest infection	Cough, dirty sputum, pyrexia, positive sputum culture +/−pathogenic organism on sputum culture
Urine infection	Pyrexia, leucocytosis, pathogenic organism on urine culture
Abdominal infection	Intra-abdominal abscess formation confirmed on CT scan or at laparotomy
Other sepsis	Sepsis due to any cause other than those listed above for example, line infection
Prolonged ileus	Absence of bowel function requiring the initiation of nutritional support
Pulmonary embolus	Confirmed radiologically or at autopsy
Deep vein thrombosis	Confirmed radiologically or at autopsy
Limb ischaemia	Compromised circulation in a limb requiring a revascularisation procedure within 30 days of surgery
Major limb amputation	Amputation of a limb due to unsalvageable critical ischaemia within 30 days of surgery
Renal infarction	New renal infarction on post-operative imaging
Renal impairment	Post-operative ≥20% increase in serum creatinine from pre-operative baseline

CPAP – continuous positive airway pressure; IPPV – intermittent positive pressure ventilation.

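### If the pre-planned leg stimulus is introduced, the primary safety endpoint still counts only events in the cuffed arm, and leg events are left to a secondary list with a narrower ischaemia definition

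*Protocol article*

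**What the plan says.** The stimulus in force is a cuff on one upper limb. The Intervention section adds an adaptive clause: if an interim analysis after 200 randomised patients shows no sign of benefit, "the stimulus will be adjusted to include three cycles of 5 minutes lower limb ischaemia alternating with 5 minutes reperfusion", run in parallel with the arm cycles. One consequential change is named: "If this augmented stimulus is introduced, bilateral ankle-brachial pressure indices <0.8 will be added to the exclusion criteria". On authority, the section says: "The decision to amend the protocol will be made by the Trial Management Committee following advice from the Data Monitoring Committee".

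The section headed Primary safety endpoint states the scope in general terms: "The primary safety endpoint will again be a composite of major life- or limb-threatening adverse events that could be attributed to the preconditioning stimulus". It then lists two components. The first is acute ischaemia, defined as "the development of ischaemia in the arm used for the preconditioning stimulus requiring systemic anti-coagulation, radiological intervention or surgical intervention". The second is deep vein thrombosis (DVT) in the subclavian, axillary or brachial vein of the same arm. Of these arm events it says: "Such an event has not been reported by any of the phase 1 and 2 trials of RIPC in cardiac patients".

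On the earlier vascular trials that used the leg, the Intervention section reports: "In these trials, four patients in the RIPC arm developed post-operative critical lower limb ischaemia requiring intervention".

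Table 2, a secondary endpoint, includes limb ischaemia, defined as "Compromised circulation in a limb requiring a revascularisation procedure within 30 days of surgery". It also lists DVT confirmed by imaging or autopsy with no restriction of site, major amputation for ischaemia, and graft occlusion confirmed by imaging. The Final analysis section compares both the primary safety endpoints and the other complications between arms.

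**The concern.** The endpoint's scope follows the stimulus, but its components are fixed to the arm. The two agree while only an arm is cuffed. Once a leg is cuffed as well, the components no longer cover what the definition says they should. The text that pre-specifies the change adjusts eligibility for the leg and leaves the safety endpoint alone.

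The omitted limb is also the one for which the article itself reports events: none reported for the arm in the cardiac trials, four for the leg in the vascular trials. If the clause is invoked, the headline safety result would describe one of two cuffed limbs. The pilot is meant to inform a phase 3 decision, possibly with the combined stimulus, since the Strengths section presents evaluation of that stimulus as an advantage of the design.

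**Working it through.** The plan gives no figure for the safety endpoint, so there is none to reproduce. The main check is a comparison of definitions.

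**Which leg events would be counted, and where, if the clause is invoked as written**

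| Event in the cuffed leg | Primary safety endpoint | Table 2 (secondary) |
|---|---|---|
| DVT confirmed by imaging | No (arm veins only) | Yes, any site |
| Ischaemia needing revascularisation within 30 days | No | Yes |
| Ischaemia leading to major amputation within 30 days | No | Yes |
| Ischaemia with imaging-confirmed graft occlusion within 30 days, however treated | No | Yes, as graft occlusion |
| Ischaemia without graft occlusion, managed without revascularisation or amputation (for example, anticoagulation alone) | No | No |

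In the cuffed arm, ischaemia treated by anticoagulation alone would be a primary safety event. The last row is therefore the true gap in recording. The rows above it are events placed on a secondary list.

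**How many patients could be affected**

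- Planned total 400, interim at 200: 400 − 200 = 200 remaining, and 1:1 allocation gives at most 100 RIPC patients with a leg cuffed.
- The Interim analysis section waits for 30-day follow-up, and the accrual rate is not given. If, as an assumption, 40 patients are recruited meanwhile: (200 − 40)/2 = 80.

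**How often events might fall outside the primary endpoint (illustration)**

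- Aims and objectives says that all the earlier vascular trials except the 62-patient one used the leg. From Table 1, the other four randomised 82 + 40 + 40 + 70 = 232.
- The RIPC share is not stated. Assuming half: 232/2 = 116, and 4/116 = 3.4% (Clopper-Pearson 95% CI 0.9% to 8.6%). With 60% on RIPC, 4/139.2 = 2.9%; with 40%, 4/92.8 = 4.3%.
- Expected cases: 100 × 0.0345 = 3.4, or 0.9 to 8.6 over the interval; 80 × 0.0345 = 2.8.
- Chance of at least one in 100 patients, 1 − (1 − p)^100: 97% at p = 3.45%, but 61% at p = 0.95% and over 99% at p = 8.6%. In 80 patients it is 94% at the point estimate.

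All four earlier cases required intervention, so those treated by revascularisation or amputation would appear in Table 2. The calculation therefore does not measure the last row of the table above. Nothing in the article does.

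**The case against.** The strongest reply is that nothing is wrong in the design now in force. The endpoint fits the arm-only stimulus, and the leg cuff can enter only through a protocol amendment, which is the natural place for a matching safety component. The article does not say that the ankle-brachial exclusion is the only change to be made. This keeps the point conditional and small. It does not remove it, because the article writes out both the pre-planned stimulus and the full component definitions, and followed as written they do not fit together.

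A second reply is that leg harm is largely captured and compared by arm in Table 2, whose DVT item is broader than the arm definition. That is correct. A reader might infer that leg harm would go unrecorded, or that three or more cases per 100 patients would be lost. The documents do not support either reading.

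A third reply is attribution. Ischaemia of the arm after these operations points to the cuff, whereas leg ischaemia after aortic or lower limb surgery may come from the operation. Adding leg events would bring background events into the composite. This is a fair cost, but the arms are randomised and compared, and separate reporting keeps the arm component clean. A reader might also take the 3.4% as harm from the leg cuff. The article gives neither cause, nor side, nor a control-arm count, so it is a crude occurrence rate and not an excess.

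**Conclusion.** The point holds as a minor, conditional one. If the adaptive clause is invoked as written, the primary safety endpoint omits one of the two cuffed limbs and no longer matches its own stated scope. Most leg events would still be seen as secondary complications. The uncounted remainder is leg ischaemia without graft occlusion that is treated without revascularisation or amputation, and its frequency cannot be estimated from the article.

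The conclusion rests on the wording alone. The illustration of a few events in up to 100 patients, with a chance of at least one anywhere from about 61% to over 99%, further assumes an even split in the earlier trials. It also assumes that their rate carries over to this trial. Those trials enrolled open AAA, EVAR and carotid patients, whereas this one also takes lower limb revascularisation.

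**What to change.** Add one sentence to the adaptive clause: if the augmented stimulus is introduced, the primary safety endpoint extends to the leg designated for cuffing, counting acute ischaemia on the same treatment threshold as the arm (anticoagulation, radiological or surgical treatment) and DVT confirmed on duplex.

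Designate that leg before randomisation in both arms, so that the planned between-arm comparison is like for like. Where lower limb surgery is unilateral, choose the non-operated leg if it is suitable. Report the arm and leg components separately.

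With this in place, a result of no leg events would be interpretable on the arm's definition: the two-sided 95% upper limit is 1 − 0.025^(1/100) = 3.6% for 0/100, or 1 − 0.025^(1/80) = 4.5% for 0/80.

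The cost is one sentence, two endpoint components and one case record form field. The ankle-brachial indices must be measured before randomisation anyway to apply the new exclusion. Eligibility is otherwise unchanged and no patients are lost. The downside is background noise from operation-related leg events, which the control arm and separate reporting address.
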